### Eligibility criteria for AGR

Due to selective contracts only patients insured by the AOK Nordost are entitled to receive AGR. The geriatric assessment comprises the activity of daily living scale (Barthel-Index), instrumental activity of daily living, Timed “Up & Go”, Chair-Rising-Test, Tandem Stance, Berg-Balance-Scale, and handgrip strength. Eligibility criteria are:Aged 70 and olderat least two geriatric multimorbidity listed in Table 1
impairment or handicap with functional deficitsat least one of the health conditions listed in Table 2

**Table 1 Tab1:** Geriatric multimorbidity

Criteria	ICD-10 codes
Immobility	M96.8, M62.3, M62.5
cognitive impairment	G30, F00 – F07
incontinence	R32, N39, R15
decubitus ulcer	L89, L97, I83, L98
Malnutrition	R64, E41, E43, E44
Disturbances in fluid and electrolyte balance	E86, E87, R60
Depression and Anxiety	F30 – F33, F40, F41
chronic pain	R52
paraesthesia	R20, G50 – G59, G60 – G64
frailty	R54
severe visual or hearing impairment	H25, H28, H52-H54, H90, H91

**Table 2 Tab2:** Eligibility criteria for participation in AGR

Eligibility criteria	ICD-10 codes
Stroke and other cerebrovascular disorders	I60-I69
Status post fracture	S72.-
Arterial obstructive disease with amputation or other surgery	I70.-
Cox and osteoarthritis with Implantation of an endoprosthesis	M16.-, M17.-
Heart failure	I50.-
Exacerbated chronic obstructive pulmonary disease	J44.0, J44.1
Pneumonia and other respiratory tract infections	J10-J22
Other fractures and injuries	S00-T98
Other arthropathies	M00-M25
Spondylopathies and Discopathies, possibly with laminectomy	M45-M51
Coronary heart disease and other heart diseases with cardiac surgery	I05-I09; I20-I25
Delirium and other organic brain psychosis	F00-F05
Osteoporosis	M80-M81
Secondary Parkinsonsyndrom	G20.9
Symptoms, effecting the nervous system and musculoskeletal system	R29.5, R29.6, R29.8

Patients are not eligible for AGR if the assessment indicates a need for hospital admission, if they are not able to participate due to a poor health status or if they are unable to provide informed consent.

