### Sample size

The intervention group consists of all AGR participants, receiving the AGR in Mecklenburg-Vorpommern during the years 2009–2013. This will comprise approximately 700 patients. Controls will be chosen from a pool of around 250.000 members of the AOK Nordost aged 70 years and older. Approximately 2800 controls will be selected from the pool.

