### Matching and statistical analyses

To balance the distribution of potential confounders among cases and controls we will conduct a propensity score matching using a many-to-one matching [16]. Variables for the estimation of the propensity score will be selected based on their expected importance to predict AGR participation as well as the outcomes of interest.

We will perform a two-step matching process. In the first step, for all patients who received AGR in a determined billing period, we plan to match controls with similar morbidity and cost characteristics during a.) the four billing periods prior to the index period in which the intervention took place, and b.) by additionally including the index period in the matching. This first step allows for the definition of an index period in controls. Using variables during the index billing period is complicated by the fact that no information on the temporal sequence of events within a billing period is available due to legally obliged data protection agreements. However, ignoring the index period may lead to a systematic ignorance of events leading to AGR which might have taken place in the index period. Therefore results from both analysis scenarios (a., b.) will be systematically compared. The first-step will be conducted as an exact match (pre matching) on selected variables listed in Table 6. These variables were selected due to their high expected conceptual importance for the estimation of treatment effects. Should no adequate numbers of controls be found, a more lenient matching may be employed. Controls will be drawn with repetition across billing periods. We plan to match up to 100 controls per case at this stage.

**Table 6 Tab6:** Matching criteria

Matching Criterion	Pre Matching	Propensity Score
Age	x ± 2 years	x
Sex	x	x
Area of residence		x
Days being insured		x
Level of nursing care	x	x
Hospital admission yes/no	x	x
Charlson Comorbidity index (CCI)		x
Days spent in the hospital		x
Hospital costs without out-of-pocket spending	x	x
Ambulatory costs		x
Costs of remedy		x
Costs of medical aid		x
Drug costs without out-of-pocket spending	x	x
Total costs with out-of-pocket spending		x
Main diagnoses before AGR		
*Musculo*-*skeletal*	x ^a^	
Status post fracture or joint replacement		
Cox- or gonarthrosis with endoprothesis		x
Other fractures and injuries		x
Other arthropaties		x
Osteoporosis		x
Spondylopathies and Discopathies, possibly with laminectomy		x
*Infection*		

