Pneumonia and other lung inflammations	x ^a^	x
*Cardio*-*vascular system*		
Heart failure		
Chronic obstructive pulmonary disease (COPD)		x
Arterial obstructive disease with amputation or other surgery	x ^a^	x
Coronary heart diseases with surgery		x
Stroke and other cerebrovascular diseases		x
*Neuro*-*psychiatric*		
Delirium and other organic brain psychosis		x
Secondary Parkinsonsyndrom	x ^a^	x
Symptoms, effecting the nervous system and musculoskeletal system		x
Charlson Comorbidity Index		
Any Malignancy	x	x
Cerebrovascular disease		x
Chronic pulmonary disease		x
Congestive heart failure		x
Metastatic solid tumor	x	
Dementia	x	x
Hemiplegia or paraplegia		x
Mild liver disease		x
Myocardial infarction		x
Renal disease		x
Peripheral vascular disease		x
Geriatric Multimorbidity		
Cognitive deficit		x
Chronic pain		x
Depression, Anxiety		x
Incontinence		x
Severe visual/hearing impairment		x
Paraesthesia		x
Immobility	x	x
Chemotherapy	x	x

^a^At least one diagnosis from each main diagnosis group will be used to match controls. Diagnoses are allowed to differ between cases and controls within the main diagnoses group

Subsequently, propensity scores will be calculated using a logistic regression model using coded morbidity and costs under the scenarios a.) and b.), based on all variables listed in Table 6, taking statistical interactions and nonlinear associations into account. Up to four controls may be assigned to one case without repetition.

Appropriate regression models (e.g. time-event models, mixed models, two-part models) will be applied to study effects on our primary and secondary outcomes. Because treatment might also affect censoring due to mortality, competing risks models (using the Fine-Gray approach) will be applied [17]. Patients dying during the follow-up period will not be excluded from the analyses.

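### Table 6 leaves out four of the eleven Table 1 geriatric criteria, frailty among them, and its unmarked fracture row conflicts with the text, so balance on these coded confounders is not ensured

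*Protocol article*

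**What the plan says.** The protocol article's section on eligibility criteria for AGR sets four conditions: age 70 or over, at least two of the Table 1 geriatric criteria, a functional deficit, and at least one Table 2 diagnosis. Table 1 has eleven criteria, each with ICD-10 codes. They include frailty (R54), "Malnutrition" (R64, E41, E43, E44), decubitus ulcer (L89, L97, I83, L98) and fluid/electrolyte disturbance (E86, E87, R60). Table 2 has fifteen diagnoses. It lists "Status post fracture" (S72) separately from other fractures and injuries (S00-T98).

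The section on matching and statistical analyses gives the selection rule: "Variables for the estimation of the propensity score will be selected based on their expected importance to predict AGR participation", and also to predict the outcomes. Table 6 then lists the matching criteria in two columns, pre-matching and propensity score. The row "Status post fracture or joint replacement" has no mark in either column. The text after the table says that the score rests on every variable the table lists. For the pre-match on main diagnosis groups, footnote a states: "Diagnoses are allowed to differ between cases and controls within the main diagnoses group".

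Under sample size, the source of controls is described as follows: "Controls will be chosen from a pool of around 250.000 members of the AOK Nordost aged 70 years and older". The exclusion criteria of Table 3 are extended to controls. The article does not say that the Table 1 criteria are.

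**The concern.** This is an observational comparison, so its credibility rests on balancing whatever drives both entry to AGR and the outcomes. A criterion that helps decide entry predicts participation by construction. Frailty, malnutrition, pressure ulcers and fluid disturbance are also plausible predictors of higher care level, nursing home admission and fracture, and prior hip fracture is an obvious candidate predictor of a new fracture. All of these are coded diagnoses of the kind the insurer supplies. The article itself uses three of the four missing conditions, at least in part of their code range, to define a secondary outcome: Table 5 lists decubitus ulcer (L89), E86 with E87.6, and malnutrition.

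As the article describes control selection, Table 6 is the main safeguard that controls resemble AGR patients on these conditions. If it leaves some out or is unclear about them, a residual difference in any of the three primary outcomes could reflect baseline differences that the data would have allowed the investigators to remove.

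**Working it through.** The article states no power, alpha or effect size on which this point depends. The check is a row-by-row comparison of the tables, followed by an illustration with assumed inputs.

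**Step 1. Table 1 against Table 6.**

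| Table 1 criterion | Row in the Table 6 geriatric block? |
|---|---|
| Immobility | yes (pre-match and score) |
| Cognitive impairment | yes |
| Incontinence | yes |
| Decubitus ulcer | **no** |
| Malnutrition | **no** |
| Fluid/electrolyte disturbance | **no** |
| Depression and anxiety | yes |
| Chronic pain | yes |
| Paraesthesia | yes |
| Frailty | **no** |
| Visual or hearing impairment | yes |

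That is 11 criteria, 7 present and 11 − 7 = 4 absent. None of the four appears elsewhere in Table 6.

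**Step 2. Table 2 against Table 6.** Of the 15 Table 2 diagnoses, 13 are marked for the propensity score. The two without a mark are status post fracture and heart failure. For heart failure, the Charlson block of Table 6 has a marked row for congestive heart failure, so little is lost. Hip fracture has no such counterpart.

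**Step 3. What happens to prior hip fracture (S72) under each reading.**

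- *The marks govern, and the other-fractures row keeps its Table 2 range.* S00-T98 contains S72, so hip fracture enters the score pooled with every injury code.
- *The marks govern, and "Other fractures and injuries" is taken to exclude S72.* Hip fracture does not enter as a diagnosis.
- *The text governs.* The row enters the score, but its label joins fracture with joint replacement, and Table 6 gives no codes for it.
- *The row is only a sub-heading.* One of the first two readings applies.

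The text reading also sits badly with the propensity-score column. If everything listed enters the score, the marks in that column have no function, yet metastatic solid tumour, for example, is marked for the pre-match only. No reading clearly gives hip fracture its own indicator.

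**Step 4. Possible scale (all inputs assumed; none is in the documents).** For one residually unbalanced binary condition with prevalence p1 in AGR patients and p0 in matched controls, and risk ratio RR with the outcome, the observed risk ratio is multiplied by

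[1 + p1(RR − 1)] / [1 + p0(RR − 1)].

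- p1 = 20%, p0 = 10%, RR = 1.5: 1.10/1.05 = 1.048
- p1 = 20%, p0 = 10%, RR = 2: 1.20/1.10 = 1.091
- p1 = 30%, p0 = 10%, RR = 3: 1.60/1.20 = 1.333
- p1 = 10%, p0 = 20%, RR = 1.5: 1.05/1.10 = 0.955
- p1 = 10%, p0 = 20%, RR = 3: 1.20/1.40 = 0.857
- equal prevalences: 1.00

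A factor above 1 would mask a benefit of AGR. A factor below 1 would exaggerate it.

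**The case against.** A reader might go further and infer that prior hip fracture is left out of the score. The documents do not support that. The text after Table 6 brings in all listed variables, and the marked row for other fractures and injuries has a range that contains S72. Osteoporosis, endoprosthesis, hospital admission, hospital days and hospital costs are marked as well. The blank cell may be a sub-heading or a mark lost when the table was read from PDF, and should be checked against the typeset table. What stands is a conflict between table and text, and a code overlap.

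A reader might also take footnote a to mean that a hip-fracture patient could end up compared with a control who has only an arthropathy. The footnote governs the first step, which gathers up to 100 candidates. The final controls, up to four, are chosen by a score that uses individual diagnoses. Nor is immobility the only Table 1 condition touched by the pre-match: dementia is pre-matched too and overlaps cognitive impairment.

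It is tempting to say that AGR patients would stay frailer than their controls and that a benefit would be hidden. The article gives no prevalences. People who need hospital admission or are too ill to take part are not eligible, so imbalance on malnutrition or pressure ulcers could run the other way. Care level, costs, the Charlson index, immobility and dementia are in the score and may balance the missing conditions in part.

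Finally, "The first-step will be conducted as an exact match (pre matching) on selected variables listed in Table 6", and those variables include hospital and drug costs without a band. The same section aims for similar, not identical, costs. Band widths are detail that an article may leave to the full protocol, so this is not part of the point.

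The Discussion does concede residual confounding. It attributes this to clinical measurements not available for controls and to motivation, which does not cover conditions that are coded in claims data.

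**Conclusion.** The point holds in a limited form. Table 6 omits four of the eleven Table 1 criteria without a stated reason and against the plan's own selection rule. That count needs no assumption. Separately, the fracture and heart failure rows are unmarked where the text says all listed variables are used, and hip fracture has no clear indicator of its own. Balance on these conditions is not ensured, which is weaker than saying they will be unbalanced.

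The size and direction of any bias cannot be derived from the documents. The factors of 1.05 to 1.33, or 0.86 to 0.96 in reverse, rest wholly on assumed prevalences of 10% to 30% and risk ratios of 1.5 to 3, for one condition with no help from correlated covariates. This is a cheap correction to make before matching. It does not show that the design fails.

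**What to change.** 1. Add frailty, malnutrition, decubitus ulcer and fluid/electrolyte disturbance to the propensity score, using the Table 1 codes.
2. Give status post fracture (S72) its own marked propensity-score row, and define the other-fractures row to exclude S72.
3. Reconcile the blank rows (fracture and heart failure) with the sentence saying that all listed variables enter the score: mark them, label them as sub-headings, or reword the sentence.
4. Report balance after matching on all eleven Table 1 criteria, under both matching scenarios (with and without the index period).

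Exact pre-matching on S72 or on the number of Table 1 conditions is a possible preference, not needed to meet this point.

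The cost is small. Table 6 marks 14 general, 13 diagnosis, 10 Charlson and 7 geriatric rows plus chemotherapy for the score: 14 + 13 + 10 + 7 + 1 = 45. Five more indicators make 50 before interactions and nonlinear terms, which about 700 cases and a pool of about 250,000 should support. No additional type of data is needed, and the target of about 2,800 controls (700 × 4) does not change.

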### Outcome measures and data collection

Claims data will comprise the billing periods from 01.01.2008 until 31.12.2014, thus ensuring a minimal observation period of 12 months prior and after the index billing period. All variables are provided for each billing period during the observation period.

The primary outcomes are ‘*progression of nursing care level*’, ‘*admission to nursing home*’ and ‘*incident fractures*’.

Four nursing care levels (0–3) are defined by the German social code XI (SGB XI). The nursing care level needs to be approved by the Medical Review Board of the statutory health insurances (MDK) in a standardised procedure. The definition for nursing care level is described in Table 4 [13]. Elderly who do not reach the requirements for nursing care level I, but need help for daily living (SGB XI § 45a) receive care for their needs. This is referred to as nursing care level 0 [13].

**Table 4 Tab4:** Definitions of the nursing care levels [13]

	Requirements	
Nursing care level	total daily help (including help in household)	personal help (included in total daily help)
1	minimum 1,5 h	>45 min
2	minimum 3 h	≥2 h, 3 times a day
3	minimum 5 h	≥4 h permanent help

The outcomes ‘*admission to nursing home*’ and ‘*incident fractures*’ are both coded as binary variables, stating whether the patients experienced the event after the index billing period or not.

Secondary outcome variables are ‘any *hospital admission*’ (yes/no), ‘*days spent in the hospital*’, ‘*ambulatory care sensitive hospital admissions*’ (yes/no) and ‘*total health care costs from the statutory health insurance perspective*’ during the entire follow-up period and during each billing period in the follow-up period. Ambulatory care sensitive hospital admissions are defined as potentially preventable hospital admissions by interventions in primary care and are displayed in Table 5. Conditions were chosen from two studies [14, 15].

**Table 5 Tab5:** Ambulatory care sensitive conditions used to define hospital admissions to be prevented by AGR (according to [14, 15])

Ambulatory care sensitive conditions	ICD-10 code
Ischaemic heart diseases	I25.0, I25.1, I25.5, I25.6, I25.8, I25.9
Heart failure	I50
Other diseases of the circulatory system	I05, I06, I08.0, I49.8, I49.9, I67.2, I67.4, I70, I73, I78, I80.0, I80.80, I83, I86, I87, I95, R00.0, R00.2
Bronchitis & COPD	J20, J21, J40-J44, J47
Mental and behavioural disorders due to use of alcohol or opioids	F10, F11

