Back pain [dorsopathies]	M42, M47, M53, M54
Hypertension	I10 - I15
Gastroenteritis and other diseases of intestines	K52.2, K52.8, K52.9, K57, K58, K59.0
Intestinal infectious diseases	A01, A02, A04, A05, A07-A09
Influenza and pneumonia	J10, J11, J13, J14, J15.3, J15.4, J15.7, J15.8, J15.9, J16.8, J18.0, J18.1, J18.8, J18.9
Ear nose throat infections	H66, H67, J01-J04, J06, J31, J32, J35
Depressive disorders	F32, F33
Diabetes mellitus	E10.2-E10.6, E10.8, E10.9, E11, E13.6, E13.7, E13.9, E14, E16.2
Gonarthrosis [arthrosis of knee]	M17.0, M17.1, M17.4, M17.5, M17.9
Soft tissue disorders	G56.0, M67.4, M71.3, M75-M77, M79
Other avoidable mental and behavioural disorders	F40, F41, F43, F45, F50.0, F50.2, F60
Diseases of the eye	H25, H40
Diseases of urinary system	N30, N34, N39.0
Sleep disorders	G47
Diseases of the skin and subcutaneous tissue	A46, L01, L02, L04, L08.0, L08.8, L08.9, L60.0, L72.1, L98.0
Thyroid disorder	E03 - E05, E89.0
Metabolic disorders	E86, E87.6
Melanoma and other malignant neoplasms of skin	C43, C44
Gastritis and duodenitis	K21, K29.7, K29.9, K30, K31
Migraine and headache syndromes	G43, G44.0, G44.1, G44.3, G44.4, G44.8, R51
Malnutrition & nutritional deficiencies	E40 - 64, R63.6, D50, D51-D52, D53.1, D56
Alcoholic liver disease	K70
Dental diseases	K02, K04-K06, K08, K12, K13
Inflammatory diseases of female pelvic organs and disorders of female genital tract	N70-N72, N75, N76, N84.1, N86, N87
Dementia	F01, F03
Diseases of male genital organs	N41, N45, N48.4
Asthma	J45
Other polyneuropathies	G62
Avoidable infectious and parasitic diseases	A15.3, A15.4, A15.9, A16.2, A16.3, A16.5, A16.8, A16.9, A34 - A37, A50-A58, A63, A64, A80, B05 - B07, B15, B16.1, B16.9, B17, B18.0, B18.1, B20 - B24, B26, B34.9, B51 - B54, B77, B86
Convulsions, not elsewhere classified	R56
Decubitus ulcer and pressure area	L89
Obesity	E66
Rare diseases with <5000 cases each	F80, R63.0, R63.3, R63.8, Z73
Cellulitis	L03, L04, L08.0, L08.8, L08.9, L88, L98.0, I891, L010, L011, L020 - L024, L028, L029
Angina	I20, I24.0, I24.8, I24.9, I25, R072, R073, R074, Z034, Z035
Convulsions and epilepsy	G25.3, G40, G41, O15, R56, R568
Dehydration and infections	A02, A04, A09, A05.9, A07.2, A08.0, A08.1, A08.3, A08.4, A08.5, E86, K52.0, K52.1, K52.2, K52.8, K52.9
Gangrene	R02

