Iron-deficiency anaemia	D46.0, D46.1, D46.3, D46.4, D50.1, D50.8, D50.9, D51.0–D51.3, D51.8, D52.0, D52.1, D52.8, D52.9, D53.1, D57.1, D58.0, D58.1, D59.0 – D59.2, D59.9, D60.1, D60.8, D60.9, D61.0, D61.1, D64.0 - D64.4, D64.8
Pelvic inflammatory disease	N70, N73, N74
Perforated/bleeding ulcer	K20, K21.0, K21.9, K22.1, K22.6, K25.0 – K25.2, K25.4 – K25.6, K25.9, K26.0 – K26.2, K26.4 – K26.6, K27,K28.0 – 28.2, K28.4 – K28.6, K92.0, K92.1, K92.2, L97
Pyelonephritis	N10, N11, N12, N13.6, N15.9, N30.0, N30.8, N30.9, N39.0,
Atrial fibrillation and flutter	I47.1, I47.9, I49.5, I49.8, I49.9, R00.0, R00.2, R00.8
Constipation	K59.0
Deliberate self-harm	S16
Dyspepsia and other stomach function disorders	K21, K30
Hypokalaemia	E87.6
Neuroses	E10, E13.6 – E13.9, E14.9
Tuberculosis	A15, A16, A17, A18, A19
Schizophrenia	F20, F21, F23.2, F25
Stroke	I61, I62, I63, I64, I66, I67.2, I69.8, R47.0

‘*Total health care costs*’ comprises expenditures for hospitalisation, remedies and medical aids, ambulatory costs, and medication. The variables concerning costs refer to costs excluding out-of-pocket spending except for remedies and medical aids where the available data does not allow for any separate analysis of out-of-pocket spending.

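### Table 6, which fixes the propensity-score variables, has no diabetes row although Table 5 counts diabetes admissions as secondary-outcome events, so diabetes balance is not directly targeted

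*Protocol article*

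**What the plan says.** Under Matching and statistical analyses, the protocol article states that score variables are "selected based on their expected importance to predict AGR participation as well as the outcomes of interest". It then fixes the model as "based on all variables listed in Table 6, taking statistical interactions and nonlinear associations into account".

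Table 6 contains the Charlson total as one row in the propensity-score column. A separate Charlson block itemises eleven conditions: any malignancy, cerebrovascular disease, chronic pulmonary disease, congestive heart failure, metastatic solid tumour, dementia, hemiplegia or paraplegia, mild liver disease, myocardial infarction, renal disease and peripheral vascular disease. Diabetes is not among them and has no row in any other block.

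Under Outcome measures and data collection: "Ambulatory care sensitive hospital admissions are defined as potentially preventable hospital admissions by interventions in primary care and are displayed in Table 5". Table 5 has a row for diabetes mellitus with the codes "E10.2-E10.6, E10.8, E10.9, E11, E13.6, E13.7, E13.9, E14, E16.2". A later row, labelled Neuroses, carries "E10, E13.6 – E13.9, E14.9", which overlaps with the E10, E13 and E14 entries of the diabetes row.

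**The concern.** The list of score variables is stated outright, so this is not a detail left open for a later plan. By itemising eleven Charlson conditions, the article treats the total as insufficient for those conditions. It gives no reason for handling diabetes differently, although a diabetes admission is itself an event for a secondary outcome.

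If diabetes were more or less common among AGR participants than among their matched controls, part of any difference in ambulatory care sensitive admissions would reflect that imbalance and not the intervention. A reader could not tell, because nothing in the matching specification aims at diabetes directly.

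**Working it through.** **1. Row check.** None of the eleven Charlson rows in Table 6 is diabetes, and no other row of the table is. Tables 1 and 2 (entry criteria) contain no E10-E14 code, so no row derived from the entry criteria carries the diagnosis. Table 3 does not exclude patients with diabetes, so they are in the analysed population.

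**2. What the Charlson total can carry.** Write the total as a weighted sum over listed conditions, diabetes and other unlisted conditions:

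CCI = Σ w(listed)·X + w(diabetes)·D + Σ w(other)·U

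Ten of the eleven listed conditions are marked in the propensity-score column. The eleventh, metastatic tumour, is marked for pre-matching. With those held fixed, the CCI term varies only with D and U.

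- If the total includes diabetes, diabetes can be swapped only for other unlisted components, not for, say, infarction or renal disease.
- If the total does not include diabetes, Table 6 holds no direct information on the diagnosis.

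The article does not say which case applies.

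**3. Partial proxies in Table 6.** "Drug costs without out-of-pocket spending" is in both the pre-matching and the score. So are hospital costs and hospital admission yes/no. Ambulatory costs, hospital days, renal disease, peripheral vascular disease and paraesthesia (neuropathy codes G60-G64 in Table 1) are in the score. These reflect disease burden and not the diagnosis, so they may balance diabetes but do not guarantee it.

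**4. Illustrative size.** The article gives no prevalence, imbalance or effect size for diabetes, so every input here is an assumption: prevalence in controls p0 = 0.30, residual imbalance of 0, 5 or 10 percentage points, and risk ratio RR of 1.2 to 2.0 for an ambulatory care sensitive admission.

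Bias factor = (1 + p1(RR − 1)) / (1 + p0(RR − 1))

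| p1 − p0 | Standardised difference | RR 1.2 | RR 1.5 | RR 2.0 |
|---|---|---|---|---|
| 0 | 0 | 1.000 | 1.000 | 1.000 |
| 0.05 | 0.107 | 1.07/1.06 = 1.009 | 1.175/1.15 = 1.022 | 1.35/1.30 = 1.038 |
| 0.10 | 0.211 | 1.08/1.06 = 1.019 | 1.20/1.15 = 1.043 | 1.40/1.30 = 1.077 |

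The standardised difference is (p1 − p0)/√[(p0(1 − p0) + p1(1 − p1))/2]. An imbalance in the other direction moves the factor below 1; for example, p1 = 0.20 and RR 2.0 give 1.20/1.30 = 0.923.

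**5. Effect on the planned size.** About 700 cases with up to four controls each gives 700 × 4 = 2,800, which reproduces the article's figure. An added score term leaves this target unchanged.

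**The case against.** The strongest reply has four parts.

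- **A Table 5 entry does not by itself require a Table 6 row.** Hypertension, thyroid disorders and sleep disorders are also in Table 5 without a row of their own. This stands. The point rests on the Table 5 entry taken together with the itemised Charlson block and the article's own selection rule.
- **No link to participation is documented.** Diabetes is in neither entry list, so the article gives no reason to expect that it predicts AGR participation, and a variable unrelated to participation given the other matched variables does not confound. This stands as a reason for low priority. It does not show that balance will be achieved.
- **Diabetes is not invisible to the score.** A reader might infer that it is matched solely through one summed index, in which it can be exchanged for any comorbidity of equal weight. Steps 2 and 3 of the working show that this goes too far: the listed conditions have their own terms, and several cost, utilisation and diagnosis rows are partial proxies.
- **The Discussion concedes residual confounding and leaves methods open to the properties of the data.** That concession concerns clinical measurements and motivation, which claims data lack. Diagnoses are in the claims data according to Study design, and the authors already use diabetes codes to define an outcome. The concession therefore does not cover this gap, though it leaves room to close it.

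**Conclusion.** The gap is real but small. Diabetes helps to define a secondary outcome, is available in the data, and has no row in the list that fixes the propensity score. It is captured indirectly at most, and its balance is not directly targeted.

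Neither the size nor the direction of any bias follows from the article. It is nil if the proxies balance diabetes. Under the assumptions in the working it is about 1 to 8% on the ambulatory care sensitive admission ratio at an imbalance of 5 to 10 points. That range treats the risk ratio as if nothing else were adjusted for; given the other matched variables, a smaller ratio would be expected.

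A reader might go further and infer that diabetes is a major driver of costs and falls, so that the primary outcomes are at risk. The article says nothing of the kind. Its only documented link is to ambulatory care sensitive admissions, and no text ties diabetes to nursing care level, nursing home admission or fractures.

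**What to change.** Add one row to Table 6, marked in the propensity-score column only: diabetes mellitus, ICD-10 E10-E14, yes/no, optionally split into with and without complications. Use the same time window as for the other diagnoses: the four billing periods before the index period in scenario a, with the index period added in scenario b. State whether the Charlson total includes diabetes. Report diabetes prevalence and the standardised difference after matching in both scenarios.

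The cost is one or two extra indicators in a logistic model with about 700 cases, from diagnoses already supplied. Leaving the row out of the pre-matching column means that no controls are lost at that step.
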